Within this framework, TABLET TOSCANA aims to develop innovative organizational models that foster the continuity of care through tele-rehabilitation for neuro-psychomotor and language functions using Khymeia technological devices in subjects with congenital and acquired developmental disabilities. Particularly, organizational dimensions, acceptability, the usability of proposed solutions, and the performance of the involved ICT, unrelated to the effectiveness of tele-rehabilitation, will be assessed as the primary objective of the study, differently from traditional literature. In addition, the secondary objective will be to evaluate the clinical effectiveness of the tele-rehabilitation intervention. We hypothesize that the TABLET TOSCANA project could establish a new organizational model to be implemented at the territorial level and integrated into routine clinical practice, improving the taking charge of the rehabilitation services for children with neurodevelopmental disabilities.

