### 2.3. Sample Size

Based on the annual count of children referred to the recruiting centers for clinical management and rehabilitation, a final sample of 100 subjects is deemed sufficient for conducting a *t*-test to analyze differences in primary endpoints between groups, assuming an effect size (d) of at least 0.4, a significance level (α) of 0.05, and a power (1-β) of 0.8.

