### 2.6. Outcome Measures

#### 2.6.1. Primary Outcome Measures

The acceptability and usability of ICT technologies in pediatric populations will also be assessed through the following Key Performance Indicators (KPIs), summarized in Table S1.

Service and technology KPIs:Study adherence: rate of acceptance of the participation in the study calculated as the number of eligible participants that agree to join the project;Adherence to training: total number of training sessions completed on the total number of sessions scheduled by the clinicians;Number of dropouts: number of participants that will not complete all of the study procedures;Number of sessions completed in the target time: total number of training sessions completed in the timeframe set by clinicians;Hardware and software technical problems: number of issues and malfunctioning experiments during the training sessions;Ad hoc feasibility questionnaires: according to the standard definitions of usability [49,50,51] and acceptability [52], specific items ranked on a five-point Likert scale (1 most negative, 5 most positive) will be defined. The aim will be to investigate four feasibility domains: (i) exercise customization, (ii) adaptability of home training, (iii) required effort and (iv) systems suitability. An introductory section will include both open and multiple-choice questions to collect information about the patient, the experimenter who fills out the questionnaire, and the devices and peripherals used. Three questionnaire versions will be available for different stakeholders (participants, parents, clinicians). The children’s format will be structured to be easy to understand for even the youngest participant and facial expressions shown through emoticons will help the children to assign the Likert-scale rank. Questionnaires will, therefore, be filled out at the end of the training by clinicians who administered the session, parents and participants over 6 years old and with cognitive and neuropsychological functioning, allowing full question comprehension and adequate cooperation;Medical Equipment Utilization: for each involved technology: the average time of utilization per session; the related consumables (if any)—the related power consumption;Set-up time: the time necessary for setting up the involved technologies;Training time/learning curve (for patients).

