Operational KPIs related to the impact of tele-rehab on facilities’ performances (inpatient–outpatient and at-home rehab services):Average length of hospital-facility stays: self-explanatory;Patient wait time for the first rehabilitation session;Bed turnover: number of discharges in the given time period/number of beds in the facilities during that time period;Bed occupancy rate: number of occupied beds on the total beds;Readmission rate: total readmissions on the total number of patients;Number of patients treated: self-explanatory;Number of beds dedicated: self-explanatory;Staff to patient ratio: number of staff needed per patient per session;Space requirements (in square meters) of the facilities’ surface requested for the specific treatments;Training time/learning curve (for healthcare professionals or families) in supporting patients during the rehab sessions;Physiotherapists’ mental workload: the amount and complexity of information decisions physiotherapists have to manage or make per session.

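### Sample size rests on a between-group t-test of the primary endpoints, but about 15 to 17 of the 20 primary KPIs allow no valid tele-rehabilitation versus usual-care contrast between participants

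*Protocol article*

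**What the plan says.** Section 2.3 states that "a final sample of 100 subjects is deemed sufficient". The purpose it gives for this number is a t-test "to analyze differences in primary endpoints between groups". The inputs are d = 0.4 or more, α = 0.05 and power 0.8. Allocation is 1:1 (section 2.4), so this means 50 per arm.

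The Introduction says that organisational dimensions, acceptability, usability and ICT performance, "unrelated to the effectiveness of tele-rehabilitation, will be assessed as the primary objective of the study"; clinical effectiveness is secondary. Section 2.6.1 then lists 9 service and technology KPIs and 11 operational KPIs as primary outcomes. Examples are "Hardware and software technical problems: number of issues and malfunctioning experiments during the training sessions", "Bed occupancy rate: number of occupied beds on the total beds" and "Patient wait time for the first rehabilitation session". No single KPI is named as the one the sample size refers to.

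Sections 2.1.2 and 2.4 give the experimental group (EG) tele-rehabilitation at once, while the wait-list group (WG) continues usual care from T0 to T1 and then has tele-rehabilitation up to T1 plus. Usability and acceptability questionnaires are given only when tele-rehabilitation ends. Section 2.7 analyses the questionnaires by age, diagnosis, functional profile and device. It does not name randomised arm as a factor for them.

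**The concern.** A two-sample t-test needs a value of the endpoint for each participant in each arm. For the comparison this trial makes, those values must come from T0–T1, the only period in which one arm has tele-rehabilitation and the other does not. Most of the listed KPIs have no such value in the usual-care arm, or have no participant-level value at all.

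If so, the only justification given for N = 100 describes a comparison that most primary endpoints cannot supply. A reader of the results could then believe that usability or operational findings came from a powered randomised comparison when they did not. An effect of tele-rehabilitation on bed use or floor space, in particular, cannot be isolated by randomising patients within two organisations that treat both arms at the same time.

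**Working it through.** **Step 1. The plan's own figure.** Inputs from section 2.3: d = 0.4, α = 0.05, power 0.8. Sidedness is not stated; two-sided is assumed and one-sided also tried.

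- Normal formula, two-sided: n per arm = 2(1.96 + 0.842)² / 0.4² = 98.1, rounded up to 99 (198 in total). The exact t calculation gives 100 per arm (200 in total).
- One-sided: 78 per arm (156 in total).
- Paired t-test, two-sided: 52 in all, but this is not a between-group test.

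None of these gives 100 in total; 100 matches only as a number per arm. With 50 per arm, the expected z is 0.4 × √(50/2) = 2.0, so two-sided power is Φ(2.0 − 1.96) = 0.52 (exact t: 0.51). One-sided power is 0.64 (exact t: 0.63). The effect detectable with 80% power, two-sided, is d = 0.57. This mismatch is separate from the endpoint problem, but it affects what can be kept of the power statement.

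**Step 2. The 20 KPIs, sorted by whether a participant-level value exists in both arms during T0–T1.**

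| Status | KPIs | Count |
|---|---|---|
| Settled before randomisation | acceptance of participation | 1 |
| Needs the device or tele-training | training adherence; sessions within target time; technical problems; questionnaires; equipment utilisation; set-up time; patient learning curve; professional and family learning curve | 8 |
| Facility indicator | length of stay; bed turnover; bed occupancy; readmission rate; number treated; beds dedicated; space | 7 |
| Set by the wait-list, if counted to tele-rehabilitation | waiting time to first session | 1 |
| Observable in both arms | dropout; staff-to-patient ratio; physiotherapist workload | 3 |

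The first four rows give 1 + 8 + 7 + 1 = 17 of 20 without a valid contrast. If length of stay and readmission are recorded per participant, this falls to 17 − 2 = 15. Among the 9 service and technology KPIs, only dropout is clearly available in both arms. Of the three comparable KPIs, dropout is a yes/no outcome and workload belongs to the clinician, so a participant-level t-test with d = 0.4 suits neither.

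**Step 3. Precision if the KPIs are estimated instead.** For a yes/no outcome per participant, the 95% half-width is 1.96 × √(p(1 − p)/n).

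- n = 100: ±7.8 points at p = 0.8; ±9.8 points at p = 0.5.
- n = 50: ±11.1 points at p = 0.8; ±13.9 points at p = 0.5.

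The n = 100 figures assume that all 100 start tele-rehabilitation. Section 2.6.1 defines training adherence as sessions completed over sessions scheduled, which is a fraction for each participant. Its mean has half-width of about 1.96 × SD/√n, where SD is the between-participant standard deviation. The documents give no such SD.

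**The case against.** Several points on the other side stand.

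- *Some KPIs can be compared.* Dropout, staff-to-patient ratio and workload exist in both arms, and length of stay and readmission would too if recorded per participant.
- *Some exclusions depend on reading.* Section 2.1.2 describes T0–T1 as a period of either tele-rehabilitation or traditional rehabilitation, so completed and on-time sessions might be counted in usual care. The article neither says so nor rules it out. Waiting time refers to a rehabilitation session, not expressly to tele-rehabilitation, and the learning curve for professionals and families is worded in the same general way. Granting all four takes the count from 15 to 15 − 2 − 1 − 1 = 11 of 20, still a majority.
- *The article condenses a fuller protocol*, and its supplementary KPI table is not shown. The absence of a single named primary KPI is therefore not treated as an error in itself. What the article does state, a test and its power for these endpoints, conflicts with the design it describes.

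Two rescues fail. Using WG data from T1–T1 plus makes a t-test mechanically possible, but both groups have then had tele-rehabilitation, so it compares starting now with starting later. Reading the groups as device groups also permits a test, but device is a stratification factor, not a randomised one, and section 2.3 does not say this is meant.

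A reader might infer that no between-group test can be run on any primary endpoint, or that the primary objective cannot be analysed at all. The documents do not support either. A few KPIs are comparable, and section 2.7 plans descriptive, qualitative and subgroup analyses of the questionnaires that need no usual-care value.

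**Conclusion.** The concern holds as a mismatch between the sample-size justification and the primary endpoints. About 15 to 17 of the 20 primary KPIs give no valid participant-level contrast of tele-rehabilitation with usual care in T0–T1; 3 to 5 could be compared. The t-test and power in section 2.3 therefore do not apply to the primary endpoints as a set, although those endpoints remain open to description and subgroup analysis.

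The count assumes that the groups in section 2.3 are the randomised arms, that training sessions are tele-rehabilitation sessions, that the professional and family learning curve concerns tele-training, and that waiting time is counted to tele-rehabilitation. The power figures assume 50 analysed per arm with no loss.

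**What to change.** Revise sections 2.3 and 2.6.1 as follows.

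1. Remove the between-group t-test as the basis for the primary KPIs.
2. Name one participant-level feasibility endpoint, for example each participant's proportion of scheduled sessions completed. Estimate it with a 95% CI in everyone who starts tele-rehabilitation (EG in T0–T1 and WG in T1–T1 plus), pooled and by arm.
3. Justify N by the precision of that endpoint. For a mean proportion, state the assumed between-participant SD and its source, and allow for WG participants lost before they start. The ±7.8 and ±9.8 point figures can be used only for a yes/no outcome per participant with all 100 starting.
4. Report facility KPIs descriptively by facility and calendar period, and do not test waiting time to tele-rehabilitation between arms.
5. Keep EG–WG tests for the T1 clinical outcomes, where a randomised control exists, but do not carry the present power statement over to them. State about 0.51 two-sided at d = 0.4, or 80% for d of about 0.57. Power is lower for any test given to only part of the sample, because section 2.6.2 selects tests to suit each patient's profile.

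The cost is wording; the data are already planned. The facility KPIs lose their status as tested primary endpoints, and the stated power becomes less favourable.

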#### 2.1.2. Phase II

During this phase, the validation of the implemented technologies will be conducted through a wait-list study (Figure 3) with two parallel arms. One hundred subjects (comprising 80 children and 20 young adults) will be recruited from the aforementioned clinical centers. The wait-list design study will ensure that all enrolled patients will be eligible for the experimental treatment, thus avoiding issues related to equipoise.

After the identification of eligible subjects according to inclusion and exclusion criteria (described below), participants will be stratified according to several criteria, including (i) diagnosis (congenital or acquired developmental disorder group), (ii) gross motor function classification system (GMFCS) level (GMFCS I–II/GMFCS III–IV), (iii) age group (6–10/11–15/16–20/21–30), (iv) and technology utilized (APP vs. Home Kit). Then, participants will be randomly assigned to the experimental group (EG)—receiving a 3-month tele-rehabilitation immediately—or the wait-list group (WG)—continuing traditional rehabilitation care for the same duration. All subjects will be evaluated before (T0) and after (T1) the 3-month intervention period (tele-rehabilitation or traditional rehabilitation), using standardized clinical tests. Moreover, participants enrolled in the WG will be re-evaluated at the end of the 3 months of tele-rehabilitation training (T1 plus). Finally, at the end of tele-rehabilitation training, ad-hoc questionnaires will be administered to the main stakeholders to assess the systems’ usability and acceptability. The program of enrolment, interventions and assessments designed according to SPIRIT guidelines are shown in Figure 4.

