As mentioned above, after the enrolment, participants will be stratified according to several criteria, including (i) diagnosis (congenital or acquired developmental disorder group), (ii) GMFCS level (GMFCS I-II/GMFCS III–IV), (iii) age (6–10/11–15/16–20/21–30), (iv) and technology utilized (APP vs. Home Kit). Randomization, sequence generation and preparation of group allocation materials will be carried out by an independent researcher who will not be involved in the trial. Using a computer-generated set of random numbers, they will be then allocated to experimental or control groups. Participants, parents, and clinical staff will be aware of the allocation group. Pairs will be randomly divided into two groups with a 1:1 experimental/SC (wait-list) ratio. Participants assigned to the experimental group will begin treatment with technology immediately for a 3-month period, while those in the SC group will continue with their usual care.

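### Section 2.3 claims 80% power at d = 0.4 with 100 subjects; an independent two-sample t-test with 50 per arm has about 51% (two-sided) or 63% (one-sided)

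*Protocol article*

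**What the plan says.** Section 2.3 (Sample Size) presents a total of 100 as enough for a t-test that compares the two arms on the primary endpoints. Its inputs read: "assuming an effect size (d) of at least 0.4, a significance level (α) of 0.05, and a power (1-β) of 0.8". It does not say whether the test is one- or two-sided, or whether it is for independent or paired samples. It gives no correlation and no allowance for loss.

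Section 2.1.2 (Phase II) shows that the 100 is the total: "One hundred subjects (comprising 80 children and 20 young adults) will be recruited from the aforementioned clinical centers". The same section describes two parallel arms.

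Section 2.4 (Participants) gives the allocation: "Pairs will be randomly divided into two groups with a 1:1 experimental/SC (wait-list) ratio". Before that, it lists stratification by diagnosis, GMFCS level, age group and technology. It contains no rule for forming matched pairs.

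**The concern.** A standardised difference of 0.4 with 80% power and 5% two-sided alpha is a familiar case that needs roughly 100 subjects in each arm. Section 2.3 gives 100 as the sum of both arms. If the stated test is the ordinary two-sample t-test, the type II error at d = 0.4 is about 49%, where the article implies 20%.

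What is at stake is the one quantitative justification of the sample size. A reader who trusts it would believe that the trial can reliably detect between-group differences of 0.4 SD. At 80% power it can detect only differences of about 0.57 SD.

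**Working it through.** **Inputs**

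- Total N = 100 (sections 2.3 and 2.1.2), two arms, 1:1 (section 2.4), so n = 50 per arm.
- d = 0.4, alpha = 0.05, power 0.8 (section 2.3).
- Sidedness is not stated. Both cases are computed, with two-sided as the main case.

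**Step 1: power of the stated test.** For an independent two-sample t-test the noncentrality is d × √(n/2), with 2n − 2 degrees of freedom.

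- 0.4 × √(50/2) = 0.4 × 5 = 2.00, with 98 degrees of freedom.
- Two-sided: the critical value is 1.984, almost the same as the noncentrality, so power is close to one half. The noncentral t gives **50.8%** (normal approximation 51.6%).
- One-sided: the critical value is 1.661 and power is **63.4%** (normal approximation 63.9%).

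The stated 80% is not reproduced in either case.

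**Step 2: sample size that the stated inputs require.** By the normal formula, n per arm = 2 × (1.960 + 0.842)² / 0.4² = 2 × 7.85 / 0.16 ≈ 98.1, so 99. The noncentral t gives 99.08, so 100 per arm (200 in total). One-sided, the noncentral t gives 77.97, so 78 per arm (156 in total).

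**Step 3: effect detectable with 50 per arm at 80% power.** Two-sided, d = 0.566, or 0.57 rounded. One-sided, d = 0.50.

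**Step 4: which calculations come near 80%?**

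| Reading | Power at 0.4, two-sided | Fits the article? |
|---|---|---|
| Independent groups, 50 per arm | 50.8% | Yes: the design as described |
| Independent groups, 100 per arm | 80.4% | No: 100 is the total, split 1:1 |
| Paired test, 50 pairs, paired effect 0.4 | 79.2% | Only if matched pairs are meant; no matching rule or paired test is given |

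In the last row, the paired effect equals the between-group d divided by √(2(1 − ρ)), where ρ is the within-pair correlation. If d = 0.4 is the between-group effect, power with 50 pairs depends on an assumed ρ:

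- ρ = 0.5: 0.4/√1.0 = 0.40, power 79.2%.
- ρ = 0.3: 0.4/√1.4 = 0.338, power 65%.
- ρ = 0: 0.4/√2.0 = 0.283, power 50%.

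**Step 5: sensitivity to loss (assumed rates, not from the article).** With 10% loss (45 per arm), two-sided power at d = 0.4 is 46.7% and the detectable d is 0.60. With 20% loss (40 per arm), the figures are 42.4% and 0.63.

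**The case against.** The strongest defence is the word pairs in section 2.4. If participants were matched and each pair split between the arms, a paired t-test would be a between-group comparison, and 50 pairs at a paired effect of 0.4 would come within a percentage point of the stated power. Section 2.3 says only t-test, so it does not exclude this. The defence shows that the text is ambiguous, but it does not rescue the figure. The article describes stratification and gives no matching rule. The result also requires d to mean the paired effect, or a within-pair correlation near 0.5, and neither is stated.

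A second defence is that *at least* 0.4 allows for larger effects. That wording makes 0.4 the smallest effect to be powered, so larger effects do not justify the claim. Nor is this a matter left to a fuller document: the figure is printed and can be checked.

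Some stronger readings are tempting, but the article does not support them:

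- *The trial will miss a real effect about half the time, and a null result will be misread.* Section 2.3 concerns the primary endpoints, which sections 2.6.1 and 1 define as acceptability, usability and organisational indicators. Many are counts, rates or facility-level figures, and the questionnaires are completed after tele-rehabilitation. For many of them there may be no contrast between the arms at T1. The 51% describes the test named in section 2.3, not every analysis in the trial.
- *The authors confused per-arm with total, or used a within-group calculation.* More than one slip would lead to about 80%, and the article does not show which occurred.
- *Omitting a dropout allowance is itself an error.* Final sample in section 2.3 may simply mean the total, and an article may leave such an allowance to the full protocol. The loss figures are only a sensitivity range.
- *Baseline adjustment restores the power.* Outcomes with a T0 value are mainly the clinical tests, which are secondary. The gain would rest on a T0–T1 correlation that the article does not give. Section 2.6.2 also selects tests by each patient's functional profile, so one test need not be given to all 100.

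**Conclusion.** The point holds. The stated inputs and the design in sections 2.1.2 and 2.4 do not give 80% power. For independent groups with 50 per arm and d = 0.4, power is 50.8% two-sided or 63.4% one-sided, and the inputs would require 100 or 78 per arm respectively. The claim fails under either sidedness.

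This rests on reading the test as an independent two-sample t-test, which is the natural reading of a comparison between two parallel randomised arms. A matched-pairs design could come close to 80%, but only under conditions that the article does not state. The conclusion does not depend on any assumption about dropout.

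**What to change.** Keep N = 100 and restate section 2.3 along these lines: *With 50 participants per arm, an independent two-sample t-test at two-sided alpha 0.05 has 80% power to detect d = 0.57; power at d = 0.4 is 51%.* If a one-sided test was intended, say so and give the matching figures (detectable d = 0.50; 63% at d = 0.4). If a loss range is wanted, label it as assumed: at 10%, the detectable d is 0.60 and power at d = 0.4 is 47%.

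Reconcile the pairs wording in section 2.4. If participants are randomised individually within strata, replace the word. If matched pairs are really formed, describe the matching rule, name the paired test in section 2.3, and state the assumed within-pair correlation or that d is the paired effect.

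The cost is a few sentences and no extra patients. The stated sensitivity becomes less favourable.
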